## Abstract

**Background:**

Laparoscopy-assisted surgery, fast-track perioperative treatment are both increasingly used in colorectal cancer treatment, for their short-time benefits of enhanced recovery and short hospital stays. However, the benefits of the integration of the Laparoscopy-assisted surgery, fast-track perioperative treatment, and even with the Xelox chemotherapy, are still unknown. In this study, the three treatments integration is defined as "Fast Track Multi-Discipline Treatment Model" for colorectal cancer and this model extends the benefits to the whole treatment process of colorectal cancer. The main purpose of the study is to explore the feasibility of "Fast Track Multi-Discipline Treatment" model in treatment of colorectal cancer.

**Methods:**

The trial is a prospective randomized controlled study with 2 × 2 balanced factorial design. Patients eligible for the study will be randomized to 4 groups: (I) Laparoscopic surgery with fast track perioperative treatment and Xelox chemotherapy; (II) Open surgery with fast track perioperative treatment and Xelox chemotherapy; (III) Laparoscopic surgery with conventional perioperative treatment and mFolfox6 chemotherapy; (IV) Open surgery with conventional perioperative treatment and mFolfox6 chemotherapy. The primary endpoint of this study is the hospital stays. The secondary endpoints are the quality of life, chemotherapy related adverse events, surgical complications and hospitalization costs. Totally, 340 patients will be enrolled with 85 patients in each group.

**Conclusions:**

The study initiates a new treatment model "Fast Track Multi-Discipline Treatment" for colorectal cancer, and will provide feasibility evidence on the new model "Fast Track Multi-Discipline Treatment" for patients with colorectal cancer.

**Trial registration:**

ClinicalTrials.gov: NCT01080547

## Background

Achieving a better quality of life for patients through enhanced recovery and shorter hospital stays in colorectal cancer treatment is becoming increasingly important.

Compared with open surgery, laparoscopy-assisted surgery has been proved by consistent evidence as a safe and effective method of colorectal cancer treatment. It also has demonstrated the benefits in reduction of surgical injury and the improvement of short-term recovery outcome [1-4].

Fast-track perioperative treatment, which is also referred as Enhanced Recovery after Surgery (ERAS), attracted much attention since Henrik Kehlet initially raised this concept [5]. This evidence-based fast-track perioperative treatment has been used for nearly a decade. The principle of the Fast-track treatment is to gain faster and enhanced recovery after surgery, by reducing unnecessary interventions which were formally involved in perioperative treatment, like reducing the fasting periods and bed rest time. Since the first time Henrik Kehlet prompted the notion, many studies have confirmed the advantages of the Fast-track treatment, especially the advantages of accelerating the short-term recovery, reducing the postoperative morbidity, shortening the hospital stays and improving the life quality [6-14].

Nevertheless, most recent researches into laparoscopy and Fast-track treatment of colorectal cancer focus on the perioperative care, which are much more related to short-term benefits, last only 1-2 weeks perioperative. In contrast, adjuvant chemotherapy takes up around 6 months of the whole colorectal cancer treatment, but has been neglected in researches mentioned above at present. So, the thoughts of combining the laparoscopy, Fast-track perioperative treatment and adjuvant chemotherapy naturally rise up, in the attempt to gain the maximum benefits covering both short-term and long-term.

Xelox and mFolfox6 chemotherapy are currently used as two comparable effective adjuvant chemotherapies for colorectal cancer, and Xelox chemotherapy is already being widely used in colorectal cancer, as it has better manageable tolerability and similar Overall Survival(OS) [15-17] versus mFolfox6 chemotherapy.

Until now, there has been no published study researching the effects of the combination of laparoscopy, Fast-track treatment and Xelox chemotherapy, which has been focused on in this FTMDT (Fast Track Multi-Discipline Treatment) trial. And we propose the new model "Fast Track Multi-Discipline Treatment" for this combination. In view of the improved rehabilitation the three component parts bring to the colorectal cancer treatment, we aim to find a more economical and effective mode for colorectal cancer treatment through this prospective randomized controlled FTMDT-trial study.

Since it has not been established whether FTMDT is superior to conventional treatment (open or laparoscopic surgery with conventional perioperative treatment and mFolfox6 chemotherapy) in colorectal cancer treatment, the following is the present study protocol.

## Methods/Design

### Study objectives

The general objective of this FTMDT trial is to assess, synthesize and discuss the feasibility of "Fast Track Multi-Discipline Treatment" model in treatment of colorectal cancer. It can be divided into 2 questions: 1. Is it safe and effective to combine Xelox chemotherapy with laparoscopy and fast-track perioperative treatment? 2. Is laparoscopy an essential component of FTMDT and how important a role does it play?

### Study design

This FTMDT-trial is an open randomized prospective and controlled study with 2 × 2 balanced factorial design. Patients eligible for the criteria will be randomized into four study groups (1:1:1:1) according to the randomized figures generated by the SPSS 16.0, after the patients signing the informed consents: (I) Laparoscopic surgery with fast track perioperative treatment and Xelox chemotherapy; (II) Open surgery with fast track perioperative treatment and Xelox chemotherapy; (III) Laparoscopic surgery with conventional perioperative treatment and mFolfox6 chemotherapy; (IV) Open surgery with conventional perioperative treatment and mFolfox6 chemotherapy.

Chinese medical insurance system ensures that, hospitalization is suitable for payment and also for patients' interest. All patients in this study will receive hospitalized chemotherapy in each cycle.

This trial has the independent "third-party" for developing the randomization.

### Eligibility

Inclusion Criteria: patients who are 18 years and older, with pathologically confirmed colon and upper rectal cancer and signed informed consent prior to enrollment.

Exclusion Criteria: Tumors which can be resected by endoscopic mucosal resection (EMR) and endoscopic submucosal dissection (ESD), history of malignancy, bowel obstruction or intestinal perforation, evidence of metastasis through physical examination, chest roentgenogram and computed tomography of liver and pelvis, acute disease and acute attack of chronic disease, psychiatric history, spinal deformity, American Society of Anesthesiologists (ASA) score ≥ IV, mid-low rectal cancer, and pregnant woman.

Adjuvant chemotherapy will be needed for III stage or high-risk II stage pathologically established colorectal cancer. The performance status of the patients after surgery will be evaluated with the Zubrod-ECOG-WHO score, before the chemotherapy start. Patients with Zubrod-ECOG-WHO score sustain ≥ 2 within 3 months after surgery will be excluded and not have the chemotherapy.

### Discontinuance criterion

The discontinuance criterion of this clinical trial as followings: 1) the trial appears causing unexpected harm or severe adverse events to participants, or the evidence that the risks outweigh the benefits, with the discontinuance decision of the ethics committees. 2) the enrollment indicates the trial can't be finished in the period of 4 years. 3) chemotherapy will be suspended for the patients with the chemotherapy adverse events more than grade 3 according to NCI-CTC AE 3.0 (National Cancer Institute Common Terminology, Criteria for Adverse Events 3.0). And the dose will be adjusted to 75% after adverse events reduce to grade 2 or lower. The chemotherapy will be withdrawn once the severe adverse events appear again.

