### Statistical analysis

#### Sample size calculation

Hospital stay is the primary endpoint. From the evidence in the researches [13,14,22-26], we estimate the hospital stay of laparoscopic and open surgery with Fast-track perioperative treatment is 6 and 8 days. Xelox chemotherapy has at most 1 hospitalization day for each cycle followed by taking Capecitabine orally at home, for a total of 8 cycles. Therefore, we calculate the hospital stay for groups I and II at 14 and 16 days. According to our previous research [27], the hospital stay of laparoscopic and open surgery with conventional perioperative treatment is 12 and 14 days. mFolfox6 chemotherapy requires at least 3 hospitalization days for each cycle, totally 12 cycles. So, we calculate the hospital stay of III and IV group is 48 and 50 days.

With the standard deviation of 6 days of mean hospitalization days, a total sample size of 218 would have a power of > 0.85 to detect a minimum reduction of 2 days in hospital stay among the 4 groups, using a 5% significance level. The III stage or high-risk II stage account for 64% of the total colorectal cancer patients [28], and these patients need the adjuvant chemotherapy according to the NCCN Clinical Practice Guidelines in Oncology-Colon Cancer Guideline 2009 (Version 2.2009) [29]. For this trial we will enroll 340 patients and have 85 patients in each group.

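### The printed trigger for suspending chemotherapy starts above grade 3, so a first grade 3 adverse event requires no hold or dose reduction in either regimen

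*Protocol article*

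**What the plan says.** The toxicity rule is item 3 of the Discontinuance criterion section. It has three steps:

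- Suspension: "chemotherapy will be suspended for the patients with the chemotherapy adverse events more than grade 3 according to NCI-CTC AE 3.0".
- Restart: "And the dose will be adjusted to 75% after adverse events reduce to grade 2 or lower".
- Withdrawal: "The chemotherapy will be withdrawn once the severe adverse events appear again". No grade is attached to the word severe.

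The rule makes no distinction between Xelox and mFolfox6. The Adjuvant chemotherapy section and the chemotherapy rows of Table 1 give drugs, doses, intervals, cycle numbers and hospital days per cycle. They contain no toxicity rule. The capecitabine dose is printed as a range (850-1,000 mg/m2), but the range is not linked to adverse events and has no counterpart in mFolfox6.

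**The concern.** The trigger is exclusive as written: an event of exactly grade 3 is not above grade 3. The restart limit is inclusive and sits at grade 2. Grade 3 therefore falls outside both. It is not severe enough to require a hold when it first appears, but it is too severe for a suspended patient to resume, even at the reduced dose.

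The stake is patient safety. The first study question in the Study objectives asks, "Is it safe and effective to combine Xelox chemotherapy with laparoscopy and fast-track perioperative treatment". The rule governs every patient given adjuvant chemotherapy, in all four groups. A clinician who follows the printed words and one who follows the likely intention could act differently on the same grade 3 event.

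**Working it through.** No power or sample-size formula bears on this point. The check is to map each whole-number grade to what the printed rule requires, and then to look for any other text that covers grade 3.

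**The rule as printed**

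| Grade of event | New event, patient on treatment | Patient already suspended |
|---|---|---|
| 0-2 | No suspension required | May restart, at 75% of the dose |
| 3 | No suspension or reduction required (3 is not above 3) | May not restart |
| 4 and above | Suspend | May not restart |

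**The rule with the trigger at grade 3 or higher**

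| Grade of event | New event, patient on treatment | Patient already suspended |
|---|---|---|
| 0-2 | No suspension required | May restart, at 75% of the dose |
| 3 and above | Suspend | May not restart |

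In the second table the stop and restart limits meet between grades 2 and 3, and no grade is left over.

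**Does other text settle grade 3?** The withdrawal sentence does not, because it gives no grade for a severe event. The regimen descriptions do not, because they hold no toxicity rule.

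**Can the reader simply assume the inclusive meaning?** Not safely. The restart sentence in the same item uses inclusive wording. The Eligibility section also marks inclusive limits, with "American Society of Anesthesiologists (ASA) score ≥ IV" among the exclusions and, for chemotherapy, "Patients with Zubrod-ECOG-WHO score sustain ≥ 2 within 3 months after surgery will be excluded and not have the chemotherapy". Of these, the wording within the same item is the stronger evidence, since the other two are symbols in a different section.

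**How many patients does the rule govern?** The Sample size calculation supplies two inputs: "The III stage or high-risk II stage account for 64% of the total colorectal cancer patients" and "For this trial we will enroll 340 patients and have 85 patients in each group".

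- All groups: 0.64 × 340 = 217.6, about 218. This agrees with the total of 218 in the protocol's own power statement.
- Per group: 0.64 × 85 = 54.4.
- Per regimen (two groups): 2 × 54.4 = 108.8, about 109.

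The figure of 218 is a ceiling on the planning figures, because patients whose performance status stays at 2 or worse receive no chemotherapy and have not been subtracted. The article gives no grade 3 event rate for either regimen, so the number whose management depends on the wording cannot be calculated. Multiplying 218 by an assumed rate would only restate the assumption.

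**The case against.** The best defence is that nothing here is inconsistent. A patient who has just had a grade 4 event is not in the same position as one with a first grade 3 event, and it is coherent to ask for fuller recovery before re-exposure. This stands. A reader might infer from the two limits that the rule contradicts itself, but the text does not support that. That grade 3 or higher was meant remains an inference, and the article does not say whether the gap between the limits is deliberate.

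A reader might also infer that a patient with a grade 3 event has to continue at full dose. The text does not support that either. Item 3 says when suspension is mandatory. It does not forbid a hold or reduction on clinical judgement, and both regimens are said to accord with the NCCN guideline. What is established is narrower: at grade 3 the printed rule requires nothing.

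It can further be said that the full protocol may hold a dose-modification schedule and that an article need not print it. That is fair, and no missing schedule is alleged. But the article chose to print a numerical safety threshold, and the point concerns that threshold. If the full protocol has a different limit, this sentence conflicts with it.

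Finally, the article's English is loose in places, so this may be a slip of wording. That is likely, and it makes the correction easy. It does not make the printed limit safe to follow.

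No bias, loss of power or distortion of the hospital-stay comparison should be read into this. The document offers nothing from which to show any of them.

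**Conclusion.** The point holds as a minor one, on the ground of patient safety. As printed, mandatory suspension begins at grade 4, and a first grade 3 event calls for no required action in either regimen. The literal reading is certain. The intended reading is probable but inferred. The rule reaches at most about 218 patients, about 109 per regimen, assuming that the 64% share holds among those enrolled. The number of them who would have a first grade 3 event is unknown.

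**What to change.** In item 3 of the Discontinuance criterion, change the suspension trigger to grade 3 or higher (CTCAE 3.0), stated for both Xelox and mFolfox6. Keep restart at 75% after recovery to grade 2 or lower. Leave the withdrawal sentence unrestricted by type of event: limiting it to a return of the same event would narrow a safety rule. If the sponsor did intend mandatory suspension to begin only at grade 4, the text should say so.

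The change is one phrase and needs no new data or patients. It does have a price. There would be somewhat more holds and dose reductions than under the literal text. A repeated grade 3 event could also be read as the return of a severe event and lead to withdrawal. Slightly fewer cycles would then be delivered. Because the primary outcome counts hospital days per cycle (3 for mFolfox6, no more than 24 hours for Xelox, per Table 1), each undelivered cycle would also remove those days from the total. The document does not allow the size of this to be estimated.

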### Primary and secondary endpoint measures

The primary outcome measure of this FTMDT-trial is the hospital stays, which is the overall hospitalization stay during treatment including both the hospital stay for the surgery and adjuvant chemotherapy.

We define the postoperative discharge day for the patients in the trial when they meet all of the discharge criteria, 1. Good pain control: NSR (Numeric Rating Scale) ≤ 3. 2. Tolerance of solid food, no need of intravenous fluid infusion. 3. Independent activities of daily living (ADL) to preoperative care level at least [18,19].

Secondary outcome measures are as follows, 1. Quality of life according to EORTC (European Organization for Research and Treatment) QLQ-C30 and QLQ-CR38 questionnaires, with the checkpoint frame, preoperation, 1 week post operation, 3-months post surgery and 6-months post surgery. 2. Chemotherapy related adverse events according to NCI CTCAE (Common Terminology Criteria for Adverse Events) Version3.0. 3. Surgical complications mainly include injury of the ureters, intraoperative transfusion, infection of incision, anastomotic leakage and readmission. 4. Hospitalization costs are calculated from the first day in hospital to the last day that adjuvant chemotherapy is finished.

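### Chemotherapy cycles lost to toxicity shorten the primary endpoint; this cannot overturn the 34-day main contrast but can distort the 2-day laparoscopy question

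*Protocol article*

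**What the plan says.** Under Primary and secondary endpoint measures, the primary outcome is hospital stay, "which is the overall hospitalization stay during treatment including both the hospital stay for the surgery and adjuvant chemotherapy". Fewer days is the desired result. The definition gives no value to a patient who stops early, and it does not say whether admissions for toxicity or readmissions count towards the total.

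Two rules elsewhere reduce the number of cycles a patient receives:

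- Discontinuance criterion, after a first suspension and dose adjustment: "The chemotherapy will be withdrawn once the severe adverse events appear again".
- Eligibility: "Patients with Zubrod-ECOG-WHO score sustain ≥ 2 within 3 months after surgery will be excluded and not have the chemotherapy".

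The Sample size calculation builds the planned totals from surgical stay plus a fixed number of days per cycle. For fast track, "we estimate the hospital stay of laparoscopic and open surgery with Fast-track perioperative treatment is 6 and 8 days"; for conventional care, "the hospital stay of laparoscopic and open surgery with conventional perioperative treatment is 12 and 14 days". For chemotherapy, "Xelox chemotherapy has at most 1 hospitalization day for each cycle followed by taking Capecitabine orally at home, for a total of 8 cycles", and "mFolfox6 chemotherapy requires at least 3 hospitalization days for each cycle, totally 12 cycles". The planned totals are 14, 16, 48 and 50 days for groups I to IV.

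The Discussion names two comparisons: I+II against III+IV for the fast-track model, and I against II for the role of laparoscopy.

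**The concern.** Each chemotherapy cycle adds days to an outcome on which fewer days is better. A cycle lost to toxicity therefore improves the patient's score, although it is a worse clinical course. This follows from the endpoint as defined, together with the protocol's own withdrawal rule.

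The laparoscopy question is where it matters. The planned difference there is only 2 days, while the chemotherapy part of the total is 8 or 36 days. If the surgical approaches differ in how many patients start or complete chemotherapy, that difference passes straight into the contrast. An approach that leaves more patients unfit for chemotherapy would look better on total stay.

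Patients who never start raise a second problem. If *excluded* in Eligibility means only that they receive no chemotherapy, they enter the analysis with a very short total. If it means that they leave the trial or the analysis, poor recovery is removed after randomisation. These are different flaws, and the text does not settle which applies.

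**Working it through.** **Inputs (Sample size calculation).** Surgical stay 6, 8, 12 and 14 days in groups I to IV. Xelox 1 day × 8 cycles = 8 days. mFolfox6 3 days × 12 cycles = 36 days.

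**Formula.** Total stay = surgical days + days per cycle × cycles received.

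**Step 1: reproduce the planned totals.** 6 + 8 = 14; 8 + 8 = 16; 12 + 36 = 48; 14 + 36 = 50. These match exactly, and only with every cycle delivered.

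**Step 2: totals with lost cycles.**

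| Cycles received | I | II | III | IV |
|---|---|---|---|---|
| All | 14 | 16 | 48 | 50 |
| Half (4 or 6) | 10 | 12 | 30 | 32 |
| None (if counted) | 6 | 8 | 12 | 14 |

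Stopping half-way saves 4 days on Xelox (4 × 1) and 18 on mFolfox6 (6 × 3). If counted, a group III patient who is too unwell to start scores 12 days, which is better than the planned group I mean of 14.

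**Step 3: main contrast, I+II v III+IV.** Planned means are (14 + 16)/2 = 15 and (48 + 50)/2 = 49, a difference of 34 days. The rates below are assumptions.

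- 20% stop half-way in every arm: the means fall by 0.20 × 4 = 0.8 and 0.20 × 18 = 3.6, so the difference is 34 − 3.6 + 0.8 = 31.2 days.
- 20% never start, Xelox arms only: 34 + 0.20 × 8 = 35.6 days.
- 20% never start, mFolfox6 arms only: 34 − 0.20 × 36 = 26.8 days.
- To bring the difference to zero with full Xelox delivery, 34/36 = 94% of mFolfox6 patients would have to never start.

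**Step 4: laparoscopy contrast.** The difference in rates between laparoscopic and open surgery that shifts the contrast by the full 2 days is 2 divided by the days lost per affected patient. The pooled figure averages the two regimens: (8 + 36)/2 = 22 for never starting, (4 + 18)/2 = 11 for stopping half-way.

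| Comparison | Never start | Stop half-way |
|---|---|---|
| I v II | 2/8 = 25 points | 2/4 = 50 points |
| Pooled laparoscopic v open | 2/22 = 9.1 points | 2/11 = 18.2 points |
| III v IV | 2/36 = 5.6 points | 2/18 = 11.1 points |

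For example, suppose 10 points more patients never start after open surgery. I v II shrinks from 2.0 to 2.0 − 0.8 = 1.2 days. The pooled contrast moves to 2.0 − 2.2 = −0.2. III v IV moves to 2.0 − 3.6 = −1.6.

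All these figures refer to patients in whom chemotherapy is indicated, for whom the planned totals were calculated. The never-start figures also require such patients to be counted.

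**The case against.** **The main comparison is robust.** This stands. A Xelox patient can lose at most 8 days against a planned 34. A reader might infer that the endpoint rewards harm in favour of the fast-track model. The documents do not support that: each lost mFolfox6 cycle removes three times as many days, so equal losses narrow the difference, to 31.2 days in the example.

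**The named laparoscopy comparison is I v II, the least sensitive one.** This also stands. Both groups receive Xelox, and a 5-point difference in starting moves that contrast by only 0.05 × 8 = 0.4 day. The larger figure for III v IV, 0.05 × 36 = 1.8 days, belongs to a comparison that the Discussion does not name. It still matters if the 2 × 2 design is used to pool laparoscopic against open groups.

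**Poor-recovery patients may not be credited at all.** If they are excluded from analysis, they receive no short stay. The sample size step 218/0.64 = 340.6 suggests a comparison built on patients needing chemotherapy, but it does not settle the reading. Toxicity withdrawals are unaffected by this ambiguity.

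**Harm is reported elsewhere and may offset.** Adverse events and complications, including readmission, are secondary outcomes, and toxicity admissions might count in the total. Separate reporting does not change what the primary test rewards, and the protocol does not say whether those days count.

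**An analysis plan may handle stopped treatment.** It may. The point rests on the stated definition, the withdrawal rule and the full-completion totals, not on absent analysis detail.

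**Two further inferences go too far.** The Discussion expects earlier entry to chemotherapy after laparoscopic surgery with fast-track care. It does not say that more patients will start, or that laparoscopy alone is responsible. Nor can the standard deviation of 6 days be said to be too small on this ground, because the text does not say whether it already includes variation in cycle number.

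**Conclusion.** The point holds in limited form. By definition, each cycle lost to toxicity improves the primary outcome by 1 day (Xelox) or 3 days (mFolfox6), and the planned totals allow for no loss. The direction of any bias depends on which arm loses more cycles.

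The first research question is safe. The 2-day laparoscopy question is exposed: modestly for I v II (25 points of difference in never-starting), more for the pooled contrast (9.1 points) and most for III v IV (5.6 points). Days per cycle are the protocol's own. The rates are assumptions, because the protocol gives no rate of starting or completing chemotherapy, and the never-start figures depend on how *excluded* is read. The Eligibility wording and the endpoint definition must be reconciled. This should be fixed before analysis, but it does not invalidate the trial or require a different primary endpoint.

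**What to change.** Keep total stay as the primary endpoint and make these changes. None alters a clinical rule.

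1. State that all randomised patients are analysed, including those withdrawn from chemotherapy and those kept from it by performance status, and reword *excluded* in Eligibility to match. If patients needing chemotherapy are also analysed as a group, define that group by pathological stage and not by whether chemotherapy was given.
2. State whether toxicity admissions and readmissions count in the total.
3. Pre-specify surgical stay in all randomised patients as a key supportive test for the laparoscopy question. The planned 2-day difference (6 v 8, 12 v 14) is already present there, and lost cycles cannot affect it.
4. Beside total stay, report by arm the proportion of planned cycles delivered and the reasons for not starting or stopping.
5. Add a sensitivity analysis that ranks patients who die, or who do not start or complete indicated chemotherapy because of toxicity or poor recovery, below all completers.

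The cost is some extra analysis and a less simple headline result. There is also a planning cost. With 64% needing chemotherapy, expected totals over all randomised patients become 6 + 0.64 × 8 = 11.1, 8 + 5.1 = 13.1, 12 + 0.64 × 36 = 35.0 and 14 + 23.0 = 37.0 days. Mixing patients with and without chemotherapy alone contributes 36 × √(0.64 × 0.36) = 17.3 days of standard deviation in the mFolfox6 arms. That makes total stay imprecise for a 2-day contrast involving those arms, and it is a further reason for item 3.
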